## Abstract

**Background:**

This paper describes the multi-institutional prospective phase II clinical trial, **SPARK**: **S**tereotactic **P**rostate **A**daptive **R**adiotherapy utilizing **K**ilovoltage Intrafraction Monitoring (KIM). KIM is a real-time image guided radiotherapy technology being developed and clinically pioneered for prostate cancer treatment in Australia. It has potential for widespread use for target radiotherapy treatment of cancers of the pelvis, thorax and abdomen.

**Methods:**

In the SPARK trial we will measure the cancer targeting accuracy and patient outcomes for 48 prostate cancer patients who will be treated in five treatment sessions as opposed to the conventional 40 sessions. The reduced number of treatment sessions is enabled by the KIM’s increased cancer targeting accuracy.

**Discussion:**

Real-time imaging in radiotherapy has the potential to decrease the time taken during cancer treatment and reduce the imaging dose required. With the imaging being acquired during the treatment, and the analysis being automated, there is potential for improved throughput. The SPARK trial will be conducted under the auspices of the Trans-Tasman Radiation Oncology Group (TROG).

**Trial registration:**

This trial was registered on ClinicalTrials.gov on 09 March 2015. The identifier is: NCT02397317

## Background

Prostate cancer stereotactic body radiation therapy (SBRT) is becoming one of radiotherapy’s success stories. Technological advances such as the Cyberknife and Calypso have enabled the safe and accurate delivery of high radiation doses to the prostate cancer of eligible patients with high cure rates and low toxicity achieved in five treatment sessions as opposed to the typical 40. Although it is going to take several years for randomized trials comparing SBRT with conventionally fractionated treatments to report, there is already a high adoption of this technology internationally: a U.S. survey showed 64% of centres were using SBRT in 2010, with the SBRT uptake growing at ~10% per year, indicating that by now almost all U.S. centres will be utilising SBRT [1]. The clinical outcome data for prostate cancer SBRT are encouraging and maturing: the recent results of a pooled analysis of 1100 patients demonstrated excellent clinical efficacy, with biochemical disease control rates of greater than 93% at five years, as well as low patient reported toxicity [2, 3]. These excellent efficacy and toxicity profiles have led to ASTRO stating that *‘data supporting the use of SBRT for prostate cancer have matured to a point where SBRT could be considered an appropriate alternative for select patients’* [4].

There is a history of advances in radiotherapy technology improving cancer treatment outcomes. These advances are particularly evident for prostate cancer where both image guided and intensity modulated radiotherapy (IMRT) have independently demonstrated improved tumour control and lower rates of late rectal toxicity [5–8]. However, prostate motion during cancer radiotherapy may shift the tumour outside the beam, simultaneously reducing target dose and exposing normal tissues to potentially damaging radiation doses. The deleterious effects of motion for prostate cancer has led ASTRO to state that ‘*A precise ability to localize the target tumour is essential to fully benefit from SBRT techniques’* [9].

There are several solutions to account for the deleterious effects of motion during prostate cancer radiotherapy, for example the CyberKnife [10], Calypso [11, 12], RayPilot [13] and Real-Time Radiotherapy [14] systems. However, these systems use hardware that is additional to a conventional linear accelerator. A new real-time image guided radiotherapy system, Kilovoltage Intrafraction Monitoring (KIM), uses the x-ray imaging system mounted on the linear accelerator to determine the 3D position of the prostate markers, and by inference the prostate, during radiotherapy treatment. KIM has evolved through *in silico* studies [15, 16], experimental studies [17, 18], the development of a quality assurance program [19], retrospective clinical evaluations [20] and recently clinical deployment in a single institution study (NCT01742403) [21, 22] where the prostate is repositioned if the KIM-guidance system shows motion exceeding a certain threshold, typically 3 mm for 5 s for conventionally fractionated treatments and 2 mm for 5 s for SBRT treatments. The clinical success of KIM has driven the creation of the SPARK trial (NCT02397317) in which KIM will be tested in multiple institutions. This paper describes the SPARK clinical trial.

## Methods/Design

The hypotheses to be tested are that in a phase II clinical trial Stereotactic Prostate Adaptive Radiotherapy utilising KIM (the SPARK trial) improves (1) Patient dose distributions, (2) Patient treatment outcomes and (3) Cancer targeting accuracy. We will test these hypotheses by performing a 48-patient clinical trial at five sites in Australia. The study schema is shown in Fig. 1.

**Fig. 1 Fig1:**
[figure not shown]
The SPARK study schema

For each treatment session for each patient, the accumulated patient dose distributions (Fig. 2) and the targeting accuracy (Fig. 3) will be determined via paired control by comparing the measured dose and targeting error with KIM to those that would have been present in the absence of KIM.

**Fig. 2 Fig2:**
[figure not shown]
The accumulated patient dose distributions will be quantified via paired control by comparing the accumulated dose distribution from the dose planned (left) with that from KIM corrections (middle) to that which would have been delivered without KIM (right)

**Fig. 3 Fig3:**
[figure not shown]
The cancer targeting accuracy will be quantified via paired control by comparing the targeting error that would have been present without KIM (above) to the targeting error with KIM corrections (below)

### Key selection criteria

#### Inclusion

Aged 18 years or older, histologically proven prostate adenocarcinoma, low or intermediate risk disease as defined by the NCCN guidelines: [23] a) Low Risk: All of PSA < 10 ng/mL, Gleason Grade 6 AND Stage T1 or T2a b) Intermediate Risk: Any or all of PSA 10–20 ng/mL, Gleason Grade 7 OR Stage T2b-c c) Absence of high risk features (PSA > 20, T3-4, N1 or M1 disease, Gleason score 8–10) with PSA measured within 3 months prior to enrolment, ECOG Performance status 0–2, suitable for definitive external beam radiotherapy (IMRT or VMAT), ability to have three gold fiducial markers placed in the prostate.

#### Exclusion

Prior lymph node irradiation, any other systemic anti-prostate cancer therapy both proven in the metastatic setting and investigational (e.g. docetaxel, enzalutamide, note androgen deprivation therapy is allowed), prostate volume > 90 cm^3^ measured from the CT scan, patient lateral dimension >40 cm as measured at the level of the prostate from the CT scan, two fiducial markers placed closer than 1 cm as measured in the axial CT scan, fiducial migration or fewer than 3 fiducials present in the CT scan.

### Objectives

The primary objective is to quantify accumulated patient dose distributions with the KIM intervention compared to dose distributions estimated without the KIM intervention. Secondary objectives are to assess patient treatment outcomes, to perform a technology assessment of KIM to quantify the clinical practice impact, and to assess KIM cancer targeting accuracy.

### Assessments

For each visit, prostate-specific antigen (PSA), GU and GI physician-graded toxicity (RTOG scale) and patient-reported outcomes using the Expanded Prostate Cancer Index Composite (EPIC) instrument will be recorded. Where possible, and noting the limitations of retrospective comparisons, different patient cohorts and differing eligibility criteria, outcome measures will be compared with controls in participating centres and with large published series, such as the 1100-patient pooled analysis by King [2, 3] and the 477-SBRT patient series from Katz [24].

Physician-reported acute toxicity will be measured during treatment, then after treatment completion at 2 weeks, 6 weeks, 3 months, 6 months and every 6 months thereafter until 3 years after treatment. Patient reported outcomes will be at baseline, then after treatment completion at 2 weeks, 6 weeks, year 1 and year 3. Biochemical control will be assessed with PSA testing at baseline, then after treatment completion at 6 weeks, 3 months, 6 months and every 6 months thereafter until 3 years after treatment. Biochemical failure is defined using the RTOG Phoenix definition [25] (any rise in the PSA >2 ng/L above the nadir). The estimated outcome improvements will be determined by applying established dose-response models to the patient’s accumulated dose and comparing with the estimated accumulated dose distribution in the absence of the KIM intervention.

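### The biochemical failure threshold is printed in ng/L while eligibility gives PSA in ng/mL, so the written rule is 1000 times smaller than 2 on the document's own PSA scale

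*Protocol article*

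**What the plan says.** Under Assessments, the protocol article bases biochemical failure on the RTOG Phoenix definition, with a citation, and glosses it in parentheses as "any rise in the PSA >2 ng/L above the nadir". That gloss is the only numerical statement of the rule.

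Under Inclusion, PSA is given in ng/mL: low risk is "All of PSA < 10 ng/mL, Gleason Grade 6 AND Stage T1 or T2a" and intermediate risk includes "PSA 10–20 ng/mL, Gleason Grade 7 OR Stage T2b-c". The high-risk item there gives a PSA cut of 20 without a unit. The unit ng/L appears nowhere except in the failure definition.

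PSA is tested at baseline and then at "6 weeks, 3 months, 6 months and every 6 months thereafter until 3 years after treatment. Biochemical failure" is defined in the sentence that follows. That makes eight post-treatment tests: 6 weeks and 3, 6, 12, 18, 24, 30 and 36 months.

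Assessments also says that, where possible and with stated caveats, "outcome measures will be compared with controls in participating centres and with large published series". One of the series named is the pooled analysis that the Background credits with "biochemical disease control rates of greater than 93% at five years".

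**The concern.** The two units differ by a factor of 1000, and the smaller one sits in the rule that decides who has failed. The gloss counts any rise beyond the threshold and asks for no confirmation or persistence, so one small upward fluctuation at one visit is enough.

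Biochemical failure is the only disease-control measure described under Assessments. It serves the secondary objective on patient treatment outcomes, which Methods/Design also lists as the second hypothesis. If the printed rule were programmed faithfully from data recorded in ng/mL, the cut-off would be 0.002. Some recurrence-free patients would then be counted as failures, and the control rate could not be set beside series reporting above 93%.

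**Working it through.** **Unit conversion**

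- Printed threshold: 2 ng/L ÷ 1000 mL per L = 0.002 ng/mL.
- The same number on the eligibility scale: 2 ng/mL × 1000 = 2000 ng/L. Ratio: 2000 ÷ 2 = 1000.
- Against the risk boundaries under Inclusion: 0.002 ÷ 10 = 0.02%, and 0.002 ÷ 20 = 0.01%.

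**What the printed rule would detect**

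The article does not say to how many decimals PSA is reported. If values are reported in ng/mL to one decimal, the smallest possible rise is 0.1, which is 0.1 ÷ 0.002 = 50 times the threshold. To two decimals it is 0.01, or 5 times the threshold. In both cases every reported rise above nadir counts as failure. To three decimals, any rise of 0.003 or more counts.

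**How many recurrence-free patients would be misclassified**

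The article gives no figure for PSA variability, assay resolution or nadir level, so this rests on assumptions:

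- Visits: the eight post-treatment tests listed above.
- Mean PSA at month *t*: plateau + (8 − plateau) × 0.5^(*t*/half-life), in ng/mL.
- Starting value 8 ng/mL; half-life 3, 6 or 12 months; plateau 0 to 0.3 ng/mL.
- Multiplicative visit-to-visit variation with a coefficient of variation (CV) of 0 to 20%.
- Values reported to 1, 2 or 3 decimals; 20,000 simulated patients per scenario.
- Failure: at any visit, a rise above the lowest earlier value that exceeds the threshold.

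| CV | Called failures, rise >2 ng/L | Called failures, rise >2 ng/mL |
|---|---|---|
| 0% | 0% | 0% |
| 5% | 0% to about 50% | 0% |
| 10% | about 1% to 69% | below 1% |
| 20% | about 11% to 86% | below 1% to about 16% |

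Under the printed rule, the highest values come from a 0.3 ng/mL plateau reported to three decimals, or at 20% CV also from a 12-month half-life. The lowest come from a fast fall towards zero or from coarse rounding. Counting or ignoring a rise of exactly 0.002 moves the three-decimal figures by at most about 3 percentage points. Transient PSA bounces were not simulated and would raise the share under the printed rule.

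**Against the benchmark**

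Control above 93% leaves less than 100 − 93 = 7% failures from all causes at five years. At 10% CV, false failures alone under the printed rule span about 1% to 69%, so they could exceed that allowance several times over (69 ÷ 7 ≈ 10). With the ng/mL unit they stay below 1%.

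**Reach**

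The primary objective is accumulated dose. The sample size (24 intervention sessions out of 240) and the interim futility look (10 intervention events) count treatment sessions. The estimated outcome improvements come from dose-response models applied to accumulated dose. None of these uses PSA failure.

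**The case against.** The best defence is that the sentence names and cites a published definition, so the parenthesis is only a gloss and an informed reader would see the slip and apply the cited rule. That makes the likely intent easy to guess. It does not make the text right: the gloss is the only numerical rule in the article, and it conflicts with the article's own PSA scale. The cited source is not at hand, so the correction rests on the mismatch with the eligibility criteria.

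A second defence is that little depends on it. That stands in part. The outcome is secondary, the external comparison is descriptive and openly caveated, and no error rate, power figure or stopping boundary changes.

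A third is that the article condenses a fuller protocol. That does not help, because the article does not leave the definition to another document but states a number with a unit. Nothing shown indicates whether the full protocol, case report form or analysis plan repeats the slip.

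A reader might also infer that under the printed rule almost every patient would fail and the control rate would be near zero. The document does not support this. A patient whose PSA keeps falling, or is reported as flat, does not fail, and the document gives no variability or precision from which to derive a near-universal failure rate.

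**Conclusion.** Wrong as written. The printed threshold is 0.002 ng/mL, 1000 times smaller than 2 on the PSA scale used for eligibility, and nothing in the article reconciles them. This follows from the document alone.

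The practical consequence is less certain. Read literally, trivial rises could be counted as failures. The misclassified share of recurrence-free patients ranges from 0% to about 86% under the assumed half-lives, plateaus, variability and rounding. That is enough to make the planned comparison with published series unsound, but not enough to claim failure in nearly all patients. Correcting the unit removes most of the problem: under the same assumptions false failures are below 1% at a CV of 10% or less, though they reach about 16% in the most extreme case (20% CV with a 12-month half-life).

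The damage is limited to a secondary outcome. The primary dose objective, the sample size and the interim rule are untouched.

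**What to change.** In the Assessments section, change the unit of the failure threshold from ng/L to ng/mL, so that it agrees with the Inclusion criteria, and confirm the wording against the cited Phoenix definition. Then check that the full protocol and the endpoint derivation carry the same unit; they are not shown here and may already be right.

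The cost is one unit in the text and a short check. Sample size, visit schedule and data collection do not change.

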### Treatment planning

Fiducial markers will be inserted prior to treatment planning. A planning CT is necessary for all patients. MRI is strongly encouraged but not required. Table 1 shows the guidelines for the structures needing to be contoured on the patient’s CT anatomy.

**Table 1 Tab1:** SPARK organs at risk contouring guidelines

Structure name	Description
Rectum	Contour as a solid structure from recto-sigmoid junction to lower aspect of ischial tuberosities, the latter of which usually corresponds to the anorectal junction.
Bladder	Contour the whole organ as a solid structure. If CT and MR volumes disagree, use the imaging with the smaller bladder volume.
Penile bulb	Contour from MRI, if available, otherwise use CT dataset.
Prostatic urethra planning target at risk volume (PRV)	Estimate urethral position, and add 3 mm radial expansion. If IDC in situ, add 1 mm radial margin to IDC. Please note that a dedicated urethra structure (from which the Urethra_PRV is created) is desirable but not mandatory.
Neck of Femur	Contour the Left and Right NOF as solid structures to the level of the ischial tuberosity.
Remaining volume at risk (RVR)	Defined as the imaged volume within the patient, excluding any delineated OAR and the PTV. The RVR is used to identify unsuspected regions of high absorbed dose (ICRU 83).

The dose-volume constraints for the treatment planning are given in Table 2.

**Table 2 Tab2:** The treatment planning dose-volume constraints for the SPARK protocol

Constraint	Per-Protocol	Minor Variation	Major Variation
PTV D95%	36.0–36.5Gy (100%)		<36.0Gy or >36.5 Gy
PTV D98%	≥34.44 Gy (95%)	32.72– <34.44 Gy	<32.72 Gy
PTV D2%	≤38.06 Gy (105%)	>38.06–39.96 Gy	>39.96 Gy
PTV Dmax to 0.1 cc	≤38.78 Gy (107%)	>38.78–40.72 Gy	>40.72 Gy
PTV Dmax	Not within a critical structure	N/A	Within a critical structure
Rectum Dmax to 0.1 cc	≤38.06 Gy (105%)	>38.06–39.96 Gy	>39.96 Gy
Rectum V34.4 Gy	≤3 cc	>3–4 cc	>4 cc
Rectum V18.13 Gy	≤50%	>50–60%	>60%
Rectum V29 Gy	≤20%	>20–25%	>25%
Rectum V32.63 Gy	≤5%	>5–10%	>10%
Bladder Dmax to 0.1 cc	≤38.06 Gy (105%)	>38.06 or 39.96 Gy	>39.96 Gy
Bladder V34.4 Gy	≤10 cc	>10–12 cc	>12 cc
Bladder V18.13 Gy	≤50%	>50–60%	>60%
Bladder V32.63 Gy	≤10%	>10–15%	>15%
Urethra_PRV Dmax 0.1 cc	≤38.78 Gy (107%)	>38.78–40.72 Gy	>40.72 Gy
Urethra_PRV V38.0 Gy	≤5%	>5–7%	>7%
FemHead_R, FemHead_L V20 Gy	≤10 cc	>10–14 cc	>14 cc
FemHead_R, FemHead_L Dmax to 0.1 cc	≤30 Gy	>30–32 Gy	>32 Gy
PenileBulb Dmax 0.1 cc	≤36.25 Gy	n/a	n/a
PenileBulb V20 Gy	≤ 1 cc	n/a	n/a
Intermediate dose spillage: ratio of volumes receiving 50% TD to 100% TD	≤4	>4–5	>5
Conformity Index (volume receiving 36.25 Gy/volume of PTV):	≤1.1	>1.1–1.2	>1.2
RVR V36.25 Gy	≤5 cc	>5–7 cc	>7 cc

During treatment planning, the prostate volume will be assessed, patient width will be measured, and the placement, number and inter-marker distance of the fiducials will be assessed. IMRT or VMAT planning is required and both flattened and flattening filer free beams are allowed. 95% of the PTV will be treated to the prescribed dose over the course of 5 fractions. Patients will receive 7.25 Gy per fraction in 5 treatments, consisting of 1–3 fractions per week. Treatment should not be delivered on any 2 consecutive days. Treatment should be completed over a period of no more than 5 weeks. There should be a minimum of 40 h and a maximum of 8 days between fractions.

### Treatment delivery

Prior to the IMRT or VMAT delivery, a Cone Beam Computed Tomography (CBCT) scan will be acquired. The patient will be aligned to the planned treatment position based on the CBCT. KIM will be initiated just prior to treatment and will monitor the prostate position as the treatment beam is delivered. Two methods will be allowed to manage movement during treatment, couch shift and multileaf (MLC) tracking. If a couch shift adaptive strategy is used, when the prostate moves from its planned position by more than 2 mm for more than 5 s, the treatment will be interrupted and the patient realigned based on the KIM software so that the prostate target is aligned to its planned position. Lower action thresholds and more frequent corrections are allowed at the discretion of the treatment team. If an MLC tracking adaptive strategy is used, the beam will continually be adjusted to target the prostate tumour.

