### Sample size calculation

We will enrol 48 patients to test the hypothesis that patient dose distributions are improved with the use of the KIM technology. The derivation follow: treating each treatment session as an independent event and then using Simon’s two-stage design, a sample size of 24 sessions with intervention events will give us 90% power with 95% confidence to rule in a success rate of 2/3 in favour of the futile rate of 1/3. To obtain an estimated 24 treatment sessions with intervention events we need 24/0.10 = 240 treatment sessions, which for the 5-session SBRT regime equals 48 patients. The null hypothesis will be rejected if 16 or more responses are observed in 48 patients. This design yields a type I error rate of 0.0488 and power of 0.91 when the true response rate is 67%.

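### The count of intervention events behind the primary test depends on adaptive strategy and local threshold, while the response cut-off is a fixed number whose stated error rates hold only near 24 events

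*Protocol article*

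**What the plan says.** **Protocol article, Sample size calculation.** The unit of the primary test is the session with an intervention event: "a sample size of 24 sessions with intervention events will give us 90% power with 95% confidence". Two response rates are set against each other, and the test is meant to "rule in a success rate of 2/3 in favour of the futile rate of 1/3". One event rate for all sessions turns this into patients: "To obtain an estimated 24 treatment sessions with intervention events we need 24/0.10 = 240 treatment sessions", hence 48 patients at five sessions each. Sessions are taken as independent ("treating each treatment session as an independent event"). The decision rule is an absolute count: "The null hypothesis will be rejected if 16 or more responses are observed in 48 patients". The operating characteristics follow: "This design yields a type I error rate of 0.0488 and power of 0.91 when the true response rate is 67" per cent.

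**Protocol article, Analysis.** The interim look after 20 patients uses the same unit: about 10 events in 100 sessions, with possible stopping for futility at four or fewer responses. Stopping is something to be considered, not required.

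**Protocol article, Treatment delivery.** Two adaptive strategies are allowed, with no expected split. Under couch shift, treatment is interrupted and the patient realigned when the prostate is displaced by more than 2 mm for more than 5 s, and "Lower action thresholds and more frequent corrections are allowed at the discretion of the treatment team". For the other strategy: "If an MLC tracking adaptive strategy is used, the beam will continually be adjusted to target the prostate tumour". No trigger is given for it.

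**The concern.** The sample size, the interim rule and the final rule all rest on one quantity, the number of sessions with an intervention event. The article ties a countable intervention to only one of its two strategies and lets local teams intervene more often under that one. Two things can then move for reasons other than KIM's effect on dose:

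- **The number of events.** If MLC-tracked sessions are left out, it falls below 24. If teams correct at lower thresholds and each correction counts, it rises above 24.
- **The motion in those events.** Sessions corrected for smaller displacements plausibly have less dose benefit to show. The article gives no figure for this, so I put no size on it.

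A cut-off fixed as a number of responses has its stated type I error and power only at the event number for which it was derived. With fewer events an effective technique may miss the cut-off. With more, a technique at the futile rate may pass it. A response rate pooled over strategies would also be hard to interpret.

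**Working it through.** **Inputs from the article.** Response rates p0 = 1/3 and p1 = 2/3, 24 events, 10% event rate, 240 sessions, 48 patients, 5 sessions each, interim at 10 events with possible stopping at 4 or fewer responses, stated type I error 0.0488 and power 0.91.

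**Assumptions of mine.** The article gives no MLC share and no event rate under lower thresholds. I use 10 or 5 of 48 patients on MLC tracking with their sessions not counted, and, separately, a doubling of the event rate to 20%.

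**Formulas.** For E events and cut-off R:

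- stop applied: P(reject) = Σ over x = 5..10 of P[Bin(10, p) = x] × P[Bin(E − 10, p) ≥ R − x]
- stop not applied: P(reject) = P[Bin(E, p) ≥ R]

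**Step 1: reproduce the plan.** 24/0.10 = 240 and 240/5 = 48, as stated. With E = 24 and R = 12, stop applied, type I error is 0.0488 at p0 = 0.333 (0.0492 at exactly 1/3). Power is 0.910 at 2/3 and 0.915 at 0.67. The stated figures therefore belong to the design 4/10, 12/24. The 12 is back-calculated and is not printed in the article. The printed 16 does not give them: 16 of 24 events has type I error 0.0008 and power 0.588 with the stop, and 16 of 48 has type I error 0.17 with the stop and 0.55 without. That is a separate error. I use 12 below so that it does not add to this point.

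**Step 2: move the event number.**

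- 10 MLC patients not counted: 38 × 5 × 0.10 = 19 events.
- 5 MLC patients not counted: 43 × 5 × 0.10 = 21.5, so 21 to 22 events.
- No MLC tracking, event rate 20%: 240 × 0.20 = 48 events.

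| Events | Type I error, stop applied | Type I error, no stop | Power, stop applied | Power, no stop |
|---|---|---|---|---|
| 19 | 0.007 | 0.007 | 0.71 | 0.72 |
| 21 | 0.019 | 0.021 | 0.84 | 0.88 |
| 22 | 0.027 | 0.033 | 0.88 | 0.92 |
| 24 | 0.049 | 0.068 | 0.91 | 0.97 |
| 48 | 0.21 | 0.92 | 0.92 | 1.00 |

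(R = 12 throughout, p0 = 1/3, p1 = 2/3.)

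**Step 3: why 0.21 is a ceiling when the stop is applied.** At p = 1/3 the chance of 5 or more responses in 10 is 0.213, so type I error cannot exceed that however many events follow. The protection depends on the stop being obeyed and on the look falling at 10 events. At a 20% event rate the look after 20 patients (100 sessions) would fall at about 20 events, for which the four-or-fewer rule was not written.

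**Step 4: chance variation alone.** Even at a true 10% rate with independent sessions, the event number has standard deviation √(240 × 0.10 × 0.90) = √21.6 ≈ 4.6 around 24. A fixed response count drifts for this reason too, whatever the event definition.

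**The case against.** The strongest reply is that this is a condensed article. How a session is classed as an event is the kind of detail that a full protocol or analysis plan would carry, and neither is shown. That stands as far as the missing definition goes. It does not remove the point, because the article itself fixes the sample size, the interim rule and an absolute response count on one pooled 10% rate, next to delivery rules under which that rate can vary.

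A reader might infer more than the documents support:

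- **That an event has no meaning under MLC tracking, or that all such sessions count or none do.** The article has KIM monitoring prostate position during delivery under either strategy, and a comparison with and without KIM for every session. An excursion above 2 mm for more than 5 s can be read from an MLC session's trace. The event is undefined in the article, not undefinable. The extreme of counting every MLC session (19 + 50 = 69 events with 10 such patients) is not something that the article states.
- **That couch-shift events are wholly discretionary.** The 2 mm and 5 s action is written as a rule. Discretion runs only towards more corrections, so sites cannot push the count below what the rule gives.
- **That error control is lost altogether.** With the interim stop applied, type I error stays at or below 0.213. The figure of 0.92 requires the stop to be disregarded, which the article permits but does not plan.

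The size also depends on shares and rates that the article does not give. With few MLC patients and the standard threshold, the count stays near 24 and the loss is small.

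**Conclusion.** The point holds in a limited form. The article lets adaptive strategy and local threshold move the number of intervention events, and the motion in them, while the cut-off is a fixed response count. The stated type I error and power hold only near 24 events.

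The size ranges from modest (power 0.84 to 0.88 with the stop, if 5 patients' MLC sessions are not counted) to material (power 0.71 at 19 events, or type I error 0.21 with the stop and 0.92 without at 48 events). These figures rest on the assumed MLC shares and event rate, on a back-calculated cut-off of 12, and on the article's own assumption of independent sessions. The definition should be settled before responses are counted. Confidence is medium, because a fuller document may already settle it.

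**What to change.** For the analysis only:

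1. Define an intervention event, for both strategies, as a session whose reconstructed KIM trace without correction exceeds the protocol's own 2 mm for more than 5 s, whatever action threshold was used in delivery.
2. State the rejection cut-off for the realised number of events, not as one fixed count, and say whether it assumes that the interim stop is binding. For example, with the 4/10 stop applied, 13 of 26 events has type I error 0.042 and power 0.91, whereas 12 of 26 has type I error 0.075. Tie the interim rule to the realised event number in the same way.
3. Report response rates by strategy alongside the pooled rate.

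The first item alone is not enough, because the event number stays random under any definition. The cost is a change of wording in the protocol and analysis plan, and some re-processing of motion traces that are already needed for the dose estimate without KIM. Patient care does not change.
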